### 2.4 Determination of sample size

To carry out the sample calculation, a 12-month success rate for the CTZ paste of 86.4% was assumed. The non-inferiority limit was considered as 15%, power of 80% and significance level of 5%, which resulted in 38 teeth per group. 20% were added to this number due to possible sample losses and 40% due to the patient having more than one tooth included, resulting in a sample of 60 deciduous anterior teeth per group, totaling 120 deciduous anterior teeth.

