#### 2.5.1 Inclusion criteria

Children aged 3 to 6 years, with at least one anterior deciduous tooth with irreversible pulpitis or pulp necrosis due to caries or trauma, with at least 2/3 of root remaining, and children who have not undergone antibiotic therapy within three months previous.

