### 2.7 Randomization

The type of treatment will be randomly determined for each tooth, through a draw before the intervention. The draw will follow the order electronically generated by the randomizer.org randomization website for a balanced distribution of all teeth between the groups.

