| 1. Complete repair (=success)    | Clinically : absence of signs and symptoms.
radiographically : absence of pathological root resorption, normal width of the periodontal ligament space, absence of lesion development in the periapical region in cases of absence of lesion observed in the initial radiograph for diagnosis and total regression of the lesion when present at the beginning of treatment. |
| 2. Incomplete repair (= success) | Clinically : absence of signs and symptoms.
radiographically : absence of pathological root resorption and reduction in size of the lesion in the periapical region.                                                                                                                                                                                                         |
| 3. Failure to repair (= failure) | Clinically : signs and symptoms indicative of apical periodontitis in the acute phase.
radiographically : presence of pathological root resorption, lesion in the furcation/periapical region of unchanged size during the follow-up period, enlargement or development of a new radiographic lesion.                                                                        |

All radiographs will be standardized using adult periapical film (Kodak, Rochester, NY, USA) in the occlusal position (modified occlusal radiograph).

The same development time, intermediate wash, fixation and final wash at all evaluation times will be used to standardize radiography processing.

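### Baseline periapical lesion decides which radiographic success rule a tooth must meet, yet the draw is not stratified and the stated comparison not adjusted for it: a modest loss of precision, with a separate dilution risk from case mix

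*Protocol*

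**What the plan says.** Protocol section 2.7 allocates each tooth by a draw from one electronically generated order, using the "randomizer.org randomization website for a balanced distribution of all teeth between the groups". The balance mentioned is in numbers of teeth. No stratification factor or blocking is named.

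Section 2.5.1 admits anterior deciduous teeth "with irreversible pulpitis or pulp necrosis due to caries or trauma" and sets no condition on a periapical lesion at entry. The Summary speaks of necrotic teeth only.

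The success table in section 2.9 treats the two kinds of tooth differently. Without a lesion at entry, the requirement is "absence of lesion development in the periapical region in cases of absence of lesion observed in the initial radiograph for diagnosis". With one, complete repair needs full regression, incomplete repair (also a success) needs a smaller lesion, and a lesion of unchanged size is a failure.

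Section 2.9 also names the clinical evaluation as primary and the radiographic signs as secondary, but then bases the judgement of success or failure on both together.

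Section 2.10 compares the groups by Student's t test or Mann-Whitney test. Poisson regression is to explore the influence of variables that are not named.

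**The concern.** The same radiographic course, no change from the initial film, is a success in a lesion-free tooth and a failure in a tooth with a lesion. Baseline lesion is therefore likely to predict radiographic and combined success. A strong predictor left out of both the allocation and the stated comparison adds avoidable noise to the paste difference. That matters in a trial sized against a 15-point non-inferiority limit.

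A second, separate question is who is enrolled. If lesion-free teeth mostly succeed with either paste, they pull the overall difference towards zero. In a non-inferiority trial (section 2.2) that pull favours the conclusion being sought.

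**Working it through.** **Inputs from section 2.4.** The protocol assumes "a 12-month success rate for the CTZ paste of 86.4" per cent. It adds "The non-inferiority limit was considered as 15" per cent, then "power of 80% and significance level of 5%, which resulted in 38 teeth per group". For inflation, "20% were added to this number due to possible sample losses and 40% due to the patient having more than one tooth included". The planned size is then 60 teeth per arm.

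**Inputs assumed.** The protocol gives neither the share of teeth with a baseline lesion (q) nor the success gap between lesion-free and lesion teeth (g). I take q = 30 to 50% and g = 10 to 30 points. Overall success of 86.4% limits g: lesion-free success, 0.864 + q × g, cannot exceed 1, so at q = 50% the gap is at most 0.136/0.5 = 27 points. The 30-point gap is therefore used only with q = 30%. The 86.4% is a 12-month rate, applied here although follow-up ends at 6 months.

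**1. The plan's own sample size.** n = 2p(1−p)(z_α + z_β)²/margin², with 2 × 0.864 × 0.136 = 0.2350.
- One-sided 5%: 0.2350 × (1.645 + 0.842)²/0.0225 = 64.6, so 65 per group.
- One-sided 2.5%: 0.2350 × (1.960 + 0.842)²/0.0225 = 82.0, so 82 per group.

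The stated 38 does not reproduce from the stated inputs. The inflation step does, nearly: 38 × 1.6 = 60.8, given as 60. The rest uses 60 per arm as planned.

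**2. Chance imbalance.** SD of the between-arm difference in lesion share = √(2q(1−q)/n).
- At q = 50%, n = 60: √(0.5/60) = 9.1 points; 95% range ±1.96 × 9.1 = ±17.9 points.
- Resulting shift in the success difference = g × imbalance: ±1.8 points at g = 10, ±3.6 points at g = 20.
- A quarter of the limit is 3.75 points. At q = 50% a shift at least that large occurs in about 4.0% of trials at g = 20 (2.0% in each direction), and in under 0.1% at g = 10. At q = 30%, g = 30 it occurs in 13.5%.

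**3. Is this additional error?** The sizing SE is √(0.2350/60) = 6.3 points. The binomial variance p(1−p) already contains the between-stratum part, q(1−q)g². Unstratified type I error, simulated at a nominal one-sided 2.5%, was 2.7% in every case tried. There is no bias and no inflation.

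**4. What stratifying and adjusting recovers.** Share of variance removed = q(1−q)g²/[p(1−p)], with p(1−p) = 0.1175. Power by formula = Φ(0.15/SE − 1.96), 60 per arm, pastes truly equal.

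| q, g | Variance removed | Power by formula | Power simulated |
|---|---|---|---|
| unstratified | – | 66.9% | 68% |
| 50%, 10 | 0.0025/0.1175 = 2.1% | 67.8% | 69% |
| 50%, 20 | 0.0100/0.1175 = 8.5% | 70.7% | 72% |
| 30%, 20 | 0.0084/0.1175 = 7.1% | 70.1% | 72% |
| 30%, 30 | 0.0189/0.1175 = 16.1% | 74.4% | 76% |

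Formula and simulation agree on the gain, about 1 to 8 points. The simulated stratified test ran at 2.9 to 3.2% type I error against 2.7% unstratified, so the simulated gain is slightly flattered. All figures treat the 60 teeth as independent and complete. With 38 per arm the unstratified power by formula is 48%.

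**5. Dilution.** If lesion-free teeth do equally well with both pastes, overall deficit = q × deficit in lesion teeth. A 20-point deficit appears as 14, 12 or 10 points when 30, 40 or 50% of teeth are lesion-free, always inside the 15-point limit. With 60 per arm at 86.4% against 76.4%, SE = √((0.1175 + 0.1803)/60) = 7.0 points. The chance of declaring non-inferiority is Φ((0.15 − 0.10)/0.0705 − 1.96) = 11% at one-sided 2.5%, or 17% at one-sided 5%. A 20-point deficit across all teeth (86.4% against 66.4%) would pass in under 1% at one-sided 2.5%.

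**6. Could the lesion subgroup carry the conclusion?** At q = 50%, g = 20, about 30 lesion teeth per arm succeed at about 76.4%. The 95% half-width is 1.96 × √(2 × 0.764 × 0.236/30) = 21 points, wider than the limit itself. It could not.

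**The case against.** Simple unstratified randomisation is valid, and leaving it unstratified is neither an error nor a contradiction. Chance imbalance averages to zero and already sits in the standard error. This stands. A reader might infer that imbalance uses up about a quarter of the 15-point limit. The documents do not support that: it takes an assumed half of teeth with lesions, an assumed 20-point gap and a 95% extreme, and it would count the same variation twice.

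A reader might also blame the single list for dilution. That is wrong too. Dilution comes from eligibility and case mix, and two lists would leave it unchanged. The confinement of a deficit to lesion teeth is itself an assumption.

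Section 2.9 names the clinical evaluation as primary, and the clinical criterion for success is the same whatever the initial film shows. This also stands, so the point bears on radiographic or combined success. It keeps force because the same section rests success or failure on both sources and tabulates them together.

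Finally, the Poisson regression could include baseline lesion, and covariates are often named in an analysis plan, which is not at hand. Fair: section 2.10 does not exclude adjustment. But the group comparison it states is unadjusted, and a stratified allocation cannot be supplied afterwards by an analysis plan. Adjustment alone would, however, recover most of the precision.

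**Conclusion.** The point holds as an inexpensive improvement in precision, not as a validity defect. Teeth facing different radiographic hurdles share one unstratified draw, and the stated comparison is unadjusted. For radiographic or combined success, stratifying and adjusting would remove about 2 to 16% of the variance and raise simulated power at 60 per arm (one-sided 2.5%) from about 68% to 69-76%. This rests on assumed lesion prevalence of 30 to 50%, an assumed gap of 10 to 30 points, and independent, complete teeth. At a 10-point gap the gain is negligible.

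Dilution is a separate matter of interpretation. Its direction favours non-inferiority, and its size depends on the unknown lesion share and on the assumption that lesion-free teeth respond alike to both pastes. A reader might infer that non-inferiority should therefore hinge on the lesion teeth; the planned size cannot support that condition.

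**What to change.** - **Section 2.7:** state that the initial radiograph is read for periapical lesion before the draw, and draw from separate blocked lists for lesion present and lesion absent. Blocking is needed because stratum sizes are unknown in advance and unblocked lists would not secure balance.
- **Section 2.10:** make the paste comparison a difference in success proportions with its confidence interval, adjusted for baseline lesion, in place of the t test or Mann-Whitney test.
- **Reporting:** give the paste difference and interval by lesion status as supportive description, so that dilution can be seen. Do not make the non-inferiority conclusion depend on the subgroup.

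**Cost:** one more list and one adjusted model. The initial film is already step 1 for both groups (sections 2.8.1 and 2.8.2). The small downside is that the draw must wait until the film has been read. If enrolment has already begun, adjustment and descriptive reporting can still be adopted and keep most of the benefit.

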### 2.8 Interventions

#### 2.8.1 Group 1. NIET + CTZ Paste

In group 1, the following endodontic treatment protocol will be performed:

1. Initial X-ray
2. Perform the anesthetic technique and isolate the operative field;
3. Remove tissues with low or high speed burs and/or dentin spoon until exposing the pulp chamber;
4. Remove the roof of the pulp chamber with inactive tip drills and remove pulp debris. Wash the pulp chamber with saline solution;
5. Locate the root canals;
6. Perform a final saline cleaning of the coronary chamber and dry with sterile cotton balls;
7. Prepare the CTZ paste: The powder that makes up the CTZ paste will be manipulated in a 1:1:2 ratio (500mg of Chloramphenicol, 500mg of Tetracycline and 1,000mg of Zinc Oxide) by Formula & Action (F&A) and incorporated into

the liquid eugenol at the time of use, with the aid of a flexible spatula nº 24 and on a sterile glass plate.

8. Insert the CTZ paste and apply light pressure with cotton balls;
9. Protect the CTZ paste with a thin layer of gutta-percha. Place the slightly warmed gutta-percha and place it on the floor of the pulp chamber, carefully at the entrances of the root canals;
10. Clean the cavity with cotton balls and alcohol;
11. Perform the restoration;
12. Finally, perform the final radiograph

#### 2.8.2 Group 2. NIET + Guedes-Pinto Paste

In group 2, the following endodontic treatment protocol will be performed:

1. Initial X-ray
2. Perform the anesthetic technique and isolate the operative field;
3. Remove tissues with low or high speed burs and/or dentin spoon until exposing the pulp chamber;
4. Remove the roof of the pulp chamber with inactive tip drills and remove pulp debris. Wash the pulp chamber with saline solution;
5. Locate the root canals;
6. Perform a final saline cleaning of the coronary chamber and dry with sterile cotton balls;
7. Prepare the Guedes-Pinto paste: Place 1 cm of Rifocort®, 1 cm of Iodoform and 2 drops of Camphorated Paramonochlorophenol (PMCC), incorporate the medicines with the help of a flexible spatula nº 24 and on a sterile glass plate.
8. Insert the Guedes-Pinto paste and apply light pressure with cotton balls;
9. Protect the Guedes-Pinto paste with a thin layer of gutta-percha. Place the slightly warmed gutta-percha and place it on the floor of the pulp chamber, carefully at the entrances of the root canals;
10. Clean the cavity with cotton balls and alcohol;
11. Perform the restoration;
12. Finally, perform the final radiograph

#### 2.9 Clinical and radiographic evaluations of selected teeth

Clinical evaluations will be considered as the primary outcome and will be performed in a dental chair under the light of a reflector, using a clinical oral mirror and palpation of the affected tooth area. At the initial examination and at the 1, 3 and 6 month follow-up examinations, the following clinical data will be recorded: history of spontaneous pain indicative of apical periodontitis, presence of fistula or abscess, presence of gingival edema, and pathological mobility. As a secondary outcome, signs of radiolucency in the periapical region and pathological root resorption will be evaluated radiographically.

The clinical data collected in the initial examination and in the control of 1, 3 and 6 months after the treatment and the comparison of the initial radiograph for diagnosis with the radiographs taken in the control exams will be the basis for evaluating the success or failure of the endodontic therapy. The radiographs will be analyzed by two experienced and trained professionals, with the aid of a negatoscope. These professionals will not have any information regarding the treatment group to which each tooth belonged and, in case of doubts during the evaluation, a consensus between the examiners will be established.

The following criteria will be used to determine the success or failure of the proposed treatment, according to the work by Chan et al 15:

|                                  |                                                                                                                                                                                                                                                                                                                                                                                               |
|----------------------------------|-----------------------------------------------------------------------------------------------------------------------------------------------------------------------------------------------------------------------------------------------------------------------------------------------------------------------------------------------------------------------------------------------|
| 1. Complete repair (=success)    | Clinically : absence of signs and symptoms.
radiographically : absence of pathological root resorption, normal width of the periodontal ligament space, absence of lesion development in the periapical region in cases of absence of lesion observed in the initial radiograph for diagnosis and total regression of the lesion when present at the beginning of treatment. |
| 2. Incomplete repair (= success) | Clinically : absence of signs and symptoms.
radiographically : absence of pathological root resorption and reduction in size of the lesion in the periapical region.                                                                                                                                                                                                         |
| 3. Failure to repair (= failure) | Clinically : signs and symptoms indicative of apical periodontitis in the acute phase.
radiographically : presence of pathological root resorption, lesion in the furcation/periapical region of unchanged size during the follow-up period, enlargement or development of a new radiographic lesion.                                                                        |

All radiographs will be standardized using adult periapical film (Kodak, Rochester, NY, USA) in the occlusal position (modified occlusal radiograph).

The same development time, intermediate wash, fixation and final wash at all evaluation times will be used to standardize radiography processing.

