of drugs is used to minimize the amount of microorganisms present in the lesion or in the root canal and tissue repair is expected if the lesion is disinfected. When applied to treat necrotic pulps in deciduous teeth, it is performed without instrumenting the root canals, that is, without conventional chemical-mechanical preparation and an association of antimicrobials is deposited in the entrances of the root canals. The LSTR approach or non-instrumental endodontic treatment (NIET) therefore involves the use of an association of antimicrobial drugs and has advantages such as less time, less complexity, prevention of irritation of the periapical tissues and the germ of the permanent successor, in addition to being able to be used in deciduous teeth that present a rhizolysis process of up to more than a third of the roots. without the conventional chemical-mechanical preparation and an association of antimicrobials is deposited in the entrances of the root canals. The LSTR approach or non-instrumental endodontic treatment (NIET) therefore involves the use of an association of antimicrobial drugs and has advantages such as less time, less complexity, prevention of irritation of the periapical tissues and the germ of the permanent successor, in addition to being able to be used in deciduous teeth that present a rhizolysis process of up to more than a third of the roots. without the conventional chemical-mechanical preparation and an association of antimicrobials is deposited in the entrances of the root canals. The LSTR approach or non-instrumental endodontic treatment (NIET) therefore involves the use of an association of antimicrobial drugs and has advantages such as less time, less complexity, prevention of irritation of the periapical tissues and the germ of the permanent successor, in addition to being able to be used in deciduous teeth that present a rhizolysis process of up to more than a third of the roots.

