### 2.5.2 Exclusion criteria

Children with compromised health, with deciduous teeth with 2/3 or more root resorption, and crypt involvement.

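### Pathological root resorption is scored by presence alone while the lesion is scored by change, so a tooth that enters with such resorption can meet neither success row, whichever paste it gets

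*Protocol*

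**What the plan says.** Protocol section 2.9 names the basis of judgement: the clinical data together with the radiographs, where "the comparison of the initial radiograph for diagnosis with the radiographs taken in the control exams will be the basis". A three-row table then defines success and failure.

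- **Lesion.** Complete repair asks for "total regression of the lesion when present at the beginning of treatment", or for no new lesion if there was none at the start. Incomplete repair asks for a smaller lesion. Failure is an unchanged, larger or new lesion. All of these refer to baseline or to change.
- **Resorption.** Incomplete repair asks for "absence of pathological root resorption and reduction in size of the lesion in the periapical region", and complete repair also requires that there be no pathological resorption. The failure row begins "presence of pathological root resorption, lesion in the furcation/periapical region of unchanged size during the follow-up period". None of the rows says new or progressing.

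Entry is governed by two limits. Section 2.5.1 takes teeth "with at least 2/3 of root remaining", and section 2.5.2 excludes children "with deciduous teeth with 2/3 or more root resorption, and crypt involvement". Both concern the amount of root, and neither separates pathological from physiological resorption. The Introduction describes the technique as usable in "deciduous teeth that present a rhizolysis process of up to more than a third of the roots".

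On the hierarchy of outcomes, section 2.9 states "Clinical evaluations will be considered as the primary outcome" and makes radiolucency and pathological resorption secondary.

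**The concern.** One table applies two different rules to two radiographic findings. A lesion seen on the initial film can still lead to success if it shrinks or disappears. Pathological resorption seen on the initial film cannot, unless it is no longer visible later. If symptoms clear, the lesion regresses and resorption stops, the tooth still fits neither success row, and the paste had no part in that.

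Such teeth would lower success in both arms and pull the arms together. In a trial declared as non-inferiority with a 15% limit, this has two effects: a truly worse paste looks less bad, and the lower success rate raises the variance and costs power. The reference list suggests how the mismatch arose. The table is taken from a cohort study of immature necrotic permanent teeth, whereas this trial treats deciduous teeth that may enter with part of the root already lost.

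**Working it through.** **Step 1: trace a tooth through the rules.** Take a tooth with pathological resorption on the initial film and at least two thirds of the root left.

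- Section 2.5.1 admits it, and section 2.5.2 does not exclude it on the amount of resorption.
- Suppose that at a control visit it has no symptoms, the lesion is gone, and the resorption is visible but unchanged. Complete repair is ruled out because resorption is present, and so is incomplete repair.
- The failure row's radiographic line is met. Its clinical line (acute signs) is not, and the table does not say whether the two lines are joined by *and* or *or*. The tooth is a failure or unclassifiable, but never a success.

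**Step 2: inputs for the size.**

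- Section 2.4: CTZ success 86.4%, limit 15%, 60 teeth per group.
- Assumed here: the limit means 15 percentage points; the 5% level is one-sided (the protocol does not say); all 60 teeth per group are analysed as independent; affected teeth are scored as failures; the 86.4% contains no such teeth; and a share f, equal in both arms, is affected. The documents give no value for f, so 5%, 10% and 20% are illustrations.

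The protocol's 38 teeth per group before inflation is not needed here. With equal rates of 86.4% the usual formula gives 2 × 0.864 × 0.136 × (1.645 + 0.842)² / 0.15² ≈ 65, so 38 does not follow from the stated inputs. That is a separate matter.

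**Step 3: formulas.**

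- Observed success: pc = (1 − f) × 0.864. For a paste truly 15 points worse: pt = (1 − f) × 0.714.
- Observed deficit: d = (1 − f) × 0.15.
- Chance of declaring non-inferiority at that deficit: Φ[(0.15 − d)/SE − 1.645], with SE = √{[pc(1 − pc) + pt(1 − pt)]/60}.
- Power if the pastes are equal: Φ[0.15/SE₀ − 1.645], with SE₀ = √{2pc(1 − pc)/60}.

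**Step 4: one case in full, f = 10%.** pc = 0.7776, pt = 0.6426, d = 0.135.

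- SE = √[(0.1729 + 0.2297)/60] = 0.0819. Error = Φ(0.015/0.0819 − 1.645) = Φ(−1.46) = 7.2%.
- SE₀ = √(2 × 0.1729/60) = 0.0759. Power = Φ(0.15/0.0759 − 1.645) = Φ(0.33) = 63%.

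**Step 5: the range.**

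| f (assumed) | Highest possible success | 86.4% becomes | 15-point deficit becomes | Error at margin | Power, equal pastes |
|---|---|---|---|---|---|
| 0% | 100% | 86.4% | 15.0 | 5.0% | 77% |
| 5% | 95% | 82.1% | 14.25 | 6.1% | 69% |
| 10% | 90% | 77.8% | 13.5 | 7.2% | 63% |
| 20% | 80% | 69.1% | 12.0 | 9.7% | 55% |

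At one-sided 2.5% the pattern is the same. For f from 0% to 20%, the error goes from 2.5% to 5.3% and power from 67% to 43%.

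**The case against.** Five points can be made for the protocol.

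1. *Section 2.9 already makes comparison with the initial film the basis of judgement.* This is the best defence, and it means that section 2.9 as a whole does refer to baseline. But the specific criteria follow that sentence, and they apply change to lesions and presence to resorption. Readers are not told how comparison works for resorption, so one could score presence and another progression. The gap in the table stands.
2. *Root lost at entry may be physiological, and only pathological resorption fails.* Correct. A reader might infer that some enrolled teeth are certain failures on the day of treatment. The documents do not support that: they allow such teeth but do not show that any will be enrolled.
3. *Resorption is a secondary outcome.* Correct. A reader might infer that the primary result is compromised, but that follows only if the combined table defines the primary endpoint. Section 2.9 bases success and failure on clinical and radiographic data together. Under the primary outcome, section 2.10 plans an intention-to-treat analysis of success and failure, and the table is the only definition of those terms. The link is open, not established.
4. *An observed deficit below 15 points does not show non-inferiority.* Correct. A reader might infer that a shrunken deficit of 13.5 points passes because it lies inside the limit. The test uses a confidence bound: with 60 per group the one-sided 95% bound is 13.5 + 1.645 × 8.19 ≈ 27 points. The real effect is the modest rise in error shown above, alongside a loss of power that works against declaring non-inferiority.
5. *Teeth are randomised, film readers are blinded, and Poisson regression is planned.* These limit imbalance and reader bias. They do not prevent a dilution that acts equally in both arms, and section 2.10 does not name the regression variables.

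**Conclusion.** The point holds as a fault in a stated scoring rule. Sections 2.5.1, 2.5.2 and 2.9 together allow a tooth to be enrolled that can never be scored a success while its initial pathological resorption remains visible. The radiographic secondary outcome is affected directly; the primary analysis is affected only if the combined table is used for it.

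The size is conditional. For an assumed 5% to 20% of teeth in both arms, success is capped at 95% to 80%, the error at the 15-point margin rises from 5% to about 6% to 10%, and power under equal pastes falls from about 77% to 69% to 55%. If no such teeth are enrolled, there is no effect. The figures ignore dropout and several teeth per child. They also take a 12-month rate from a trial in primary molars as the reference for a 6-month study of anterior teeth. They show direction and order of size, and are not a forecast.

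**What to change.** Reconcile sections 2.5.1, 2.5.2 and 2.9 by scoring resorption as the lesion is scored:

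- **Success rows:** no new or progressing pathological root resorption compared with the initial radiograph.
- **Failure row:** new or progressing pathological root resorption compared with the initial radiograph.
- **Baseline item:** from the initial film already taken as the first step in both arms, record pathological resorption (none or present, and extent) as distinct from physiological resorption, and report it by arm.
- **Link to the analysis:** say in sections 2.9 and 2.10 whether this table or the clinical findings alone define success in the primary analysis.

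The cost is a change of wording and one data item, with no extra visit or film. There is one small downside: the blinded readers must judge progression and separate it from physiological resorption, so they need a written rule for that. They already judge change for the lesion.
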